The sample size of 150 mother-infant pairs per maternity is based on a series of power calculations using various prevalence estimates of the prevalence of EBF at 6 months in the control group (15% to 35% for usual care) and a minimum expected effect size of RR = 1.5 for the first objective – comparison of BFHI steps 1-9 to usual care (figure 2.a) and a prevalence of EBF at 6 months in the BFHI steps 1-9 group of 45 to 65% and a minimum expected effect size of RR = 1.3 for the second objective – comparison of the provision of support in the well-child clinics in addition to the implementation of BFHI steps 1-9 in maternities vs. BFHI steps 1-9 in maternities alone (figure 2.b). Assuming two-tailed Person chi-square test with α values of .05, the sample size of 900 mother-infant pairs should provide adequate power to detect a modest difference in the proportion of infants exclusively breastfed at 6 months between BFHI alone and usual care arms or between BFHI steps 1-9 + well-child clinics arm and BFHI steps 1-9 alone.

To determine the number of clusters of size n = 150 that will be needed to achieve an 80% power, we used the formula proposed by Hayes and Bennett (40). Assuming a coefficient of variation of 25% (which is generally considered reasonable), and a 20% prevalence of exclusive breastfeeding in the “usual care” group, we varied various expected prevalence of EBV that could be achieve with the implementation of the Ten Steps. Results are presented in the figure 3 below. Once the prevalence of EBF in the intervention group reaches 40%, the number of clusters needed falls below 4.

**Figure 2.** Power estimate curves for: a- detecting a minimum effect size of RR = 1.5 comparing the prevalence of EBF at 6 months in the BFHI steps 1-9 group to that in the usual care group and b- detecting a minimum effect size of 1.3 comparing prevalence of EBF at 6 months in BFHI steps 1-9 + well-child clinic group to that in BFHI steps 1-9 group for a sample of n = 150 per health facility, n = 300 per randomization group, and n = 900 total for various prevalences of exclusive breastfeeding at 6 months.

Figure 3. Number of clusters of size 150 needed to achieve 80% power for a fixed coefficient of variation of 0.25 by the expected proportion of EBF in the intervention group, assuming a 20% prevalence of EBF in the usual care group.

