Assuming a loss to follow-up rate of 10% over the 6 months - the duration of the follow-up in the study, the effective sample size that will be available for analysis is 135. With this effective sample size, our study will have an 88% power to detect a modest 30% increase in the prevalence of exclusive breastfeeding at 6 months in the intervention group – corresponding to a change as small as an increase from the current proportion of EBF at 6 months of 17% (assuming it stays the same in the usual care group) to 22.5% after implementing BFHI steps 1 through 9.

At the end of the evaluation, the findings of the study will be shared with all facilities that took part in the study and with the community. Facilities in the usual care arm will be encouraged to implement the most successful intervention.

1. **Sustainability and Potential for Scaling-Up**

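### The stated 88% power to detect a rise in 6-month EBF from 17% to 22.5% is wrong: the protocol's own test gives about 36% before clustering, and roughly 9–15% with it

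*Protocol*

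**What the plan says.** The sample-size text is at the end of the Evaluation section of the Protocol's Proposal Narrative. It plans 150 pairs per facility, 300 per randomised group and 900 in total. The test is fixed: "Assuming two-tailed Person chi-square test with α values of .05". The planning scenario for BFHI steps 1-9 against usual care is 15–35% EBF under usual care and "a minimum expected effect size of RR = 1.5 for the first objective". For adding well-child clinic support to BFHI steps 1-9, it is "a prevalence of EBF at 6 months in the BFHI steps 1-9 group of 45 to 65" per cent with an RR of 1.3. The number of clusters is then worked out with the Hayes and Bennett formula and a coefficient of variation of 25%.

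The loss-to-follow-up paragraph comes next: "Assuming a loss to follow-up rate of 10% over the 6 months", after which "the effective sample size that will be available for analysis is 135". From this it concludes that "our study will have an 88% power to detect a modest 30% increase in the prevalence of exclusive breastfeeding at 6 months". It gives the corresponding rates as a change "from the current proportion of EBF at 6 months of 17% (assuming it stays the same in the usual care group", and puts the BFHI steps 1-9 arm at 22.5%. The power sentence does not mention clustering. The Project Design section randomises six facilities to three groups, which is two per arm, and says that facilities will be matched on key characteristics beforehand.

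**The concern.** A 5.5-point difference between proportions near 20%, with fewer than 300 infants per arm, does not ordinarily have power close to 90%. The sentence also joins things that the preceding paragraphs keep apart. It applies an increase of about 30% to the comparison for which the RR was 1.5, and it leaves out the clustering that was allowed for one paragraph earlier.

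This is the only numerical power figure in the text for the sample after loss to follow-up, and it concerns a primary objective and a primary outcome. A funder or ethics reviewer would take from it that a gain as small as 5.5 points would very probably be detected. If BFHI steps 1-9 then showed no significant effect, the 88% could be cited as grounds for ruling out a modest benefit. The protocol ties scale-up and the national programme's efforts to these findings.

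**Working it through.** **Inputs, all from the Protocol.** Usual care p0 = 0.17; BFHI steps 1-9 p1 = 0.225; difference d = 0.055; two-sided alpha 0.05 (z = 1.96), Pearson chi-square; n = 135 per facility after 10% loss; c = 2 facilities per arm, so 270 per arm; coefficient of variation k = 0.25.

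**1. The stated figure, without clustering.** Power = Φ[(d − 1.96·SE0)/SE1], where SE0 is the pooled null standard error and SE1 the unpooled one.
- Pooled p = (0.17 + 0.225)/2 = 0.1975; SE0 = √(2 × 0.1975 × 0.8025/270) = 0.03426.
- SE1 = √((0.17 × 0.83 + 0.225 × 0.775)/270) = 0.03418.
- Power = Φ[(0.055 − 0.06716)/0.03418] = Φ(−0.356) = **36.1%**. A 200,000-run simulation gave 36.3%.

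The 88% is not reproduced. Other readings of the sentence:

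| Reading | Power |
|---|---|
| Exact 30% increase, 17% × 1.3 = 22.1%, 270 per arm | 32.0% |
| No loss, 300 per arm | 39.4% |
| 135 taken as the arm size | 20.4% |
| All 810 analysable pairs split into two arms of 405 | 50.2% |
| 810 counted as a single arm | 79.5% |
| One-sided test, 270 per arm | 48.4% |

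The nearest reading found is a one-sided test with 810 per arm (87.2%), which contradicts both the two-tailed test and the three-arm design. For 17% versus 22.5%, 88% power needs about 1,029 pairs per arm before clustering.

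**2. Checking the cluster formula against the protocol.** Hayes–Bennett: c = 1 + (1.96 + z_β)² V/d², with V = p0(1−p0)/n + p1(1−p1)/n + k²(p0² + p1²). For 20% versus 40%, n = 150, k = 0.25 and 80% power: V = 0.16/150 + 0.24/150 + 0.0625 × 0.20 = 0.01517, so c = 1 + 7.849 × 0.01517/0.04 = 3.98. This agrees with the protocol's statement that fewer than 4 clusters are needed at 40%, so the formula is being used as the protocol used it.

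**3. The same formula for 17% versus 22.5%, n = 135, c = 2.**
- V = 0.1411/135 + 0.174375/135 + 0.0625 × (0.0289 + 0.050625) = 0.00105 + 0.00129 + 0.00497 = 0.00731; √V = 0.0855.
- With the +1 term: z_β = 0.055 × √(1/0.00731) − 1.96 = −1.317, power **9.4%**.
- Without it: z_β = 0.055 × √(2/0.00731) − 1.96 = −1.050, power **14.7%**.
- Cluster-level t-test, SE = √(0.00731/2) = 0.0604, non-centrality 0.91: 8.8% on 2 df, 10.1% on 3 df.
- A cruder design-effect calculation (ICC 0.0128 from k and p0, design effect 2.7) gives about 16%.

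For 80% power the formula asks for about 20 clusters per arm.

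**4. Where 88% does appear.** With 270 per arm and no clustering, 45% versus 58.5% (RR 1.3, the low end of the second objective's range) gives 88.3%. But 25% versus 37.5% (RR 1.5, inside the first objective's range) gives 88.2%. With k = 0.25 and two facilities per arm, 45% versus 58.5% falls to 10.3% with the +1 term, 16.4% without it, and 9.4% with the t-test on 2 df.

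**The case against.** **The clustered figure depends on method.** The planned analysis is GEE with a log-binomial model, not a cluster-level t-test, and the facilities are to be matched, which may lower the effective between-facility variation. This stands, and it is why a range is given. The protocol gives no matched coefficient of variation. If matching reduced it to 0.10 (my assumption), power would be about 14–28%. Removing clustering altogether still leaves 36%.

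**The origin of the 88%.** A reader might infer that it was carried over from the second objective, since the 30% wording fits RR 1.3. That is plausible, but the protocol does not say so, and a scenario within the first objective's range gives practically the same figure.

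**RR 1.5 against a 30% increase.** A reader might call this a flat contradiction. It is not quite one: 1.5 is the minimum effect used to choose 150 per facility, while the later sentence describes a smaller detectable change. The relation needs explaining, but aligning the two would not restore the 88%: 17% × 1.5 = 25.5% gives about 68% at 270 per arm without clustering. The 0.4-point gap between 22.1% and 22.5% is minor.

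**What a null result would mean.** The analysis estimates prevalence ratios, and confidence intervals would show the imprecision. So over-reading a null result is a risk, not a certainty.

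**Conclusion.** The 88% is wrong for the rates it is attached to. Under the stated test with 270 per arm, power is about 36% (32% for an exact 30% increase; about 20% if 135 is the arm size), and no two-sided reading tried reaches 88%. With the protocol's coefficient of variation of 0.25, two facilities per arm and no allowance for matching, power is roughly 9–15%.

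The unclustered figure rests only on numbers printed in the protocol. The clustered range also depends on the method chosen and on taking 0.25 as the effective variation after matching.

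It would be too strong to say that the trial cannot detect a 5.5-point gain: 36% or 10% power means that detection is unlikely, not impossible. The error is a figure that the protocol states, not a detail left to an analysis plan.

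**What to change.** Delete the 88% sentence. In its place, state that for 17% versus 22.5% with 135 analysable pairs per facility and two facilities per arm, power is about 36% before clustering and roughly 9–15% with a coefficient of variation of 0.25. Name the method, and say that any gain from matching is not included.

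Do not keep the 88% by attaching it to 45% versus 58.5%. That figure ignores clustering too, and with the stated coefficient of variation its power is only about 9–16%.

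Explain how the 30% increase relates to the RR of 1.5 given for the first objective, and state which effect the trial is sized on.

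The change is to protocol wording only. The cost is that the stated power becomes far less favourable, and the protocol can no longer claim that a change this small would probably be detected.

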
Local field implementation of activities will be the responsibility of KSPH in collaboration with the UNC-CH In-Country Project Director. In collaboration with the In-Country Project Director, KSPH will oversee timely implementation of field activities and ensure that all activities and results requirements are met. The KSPH will be responsible for: hiring, administrative management and institutional oversight of the local hires; all local logistics support related to project activities, office operations, and local financial management; reporting of any adverse events or human subjects violations regarding IRB approved protocols; and data collection and participant interaction.

Other project contributors include non-governmental organizations such as the Armée du Salut (AS) and Bureau Diocésain des Œuvres Médicales de Kinshasa (BDOM). UNC/KSPH will select six health facilities from a network of forty-four within the DRC for the proposed study. Most of these facilities if not government owned are part of either BDOM or AS health network. AS and BDOM will also be keys partners in the dissemination and scale-up of the findings from this study. Our key partners have agreed to provide staffing and other assistance toward local field implementation on this research initiative. The Congolese MOH will act in an advisory capacity offering assistance as needed.

The KSPH/UNC-DRC partnership functions based on contractual agreements and a manual of procedures that describes the management policies and procedures regarding personnel, communications and lines of authority, and collaboration with other partners and programs. The Director of the KSPH has overall responsibility for adherence to in-country regulations, labor code, as well as USG regulations. The Director of the KSPH has also overall responsibility for monitoring, evaluation and financial management.

